#### MR-HIFU

MR-HIFU will be performed by well-trained and experienced radiologists using the latest version of the CE-marked Sonalleve MR-HIFU platform (Profound Medical Inc.) integrated into a 1.5-T MR-scanner (Achieva; Philips Healthcare) using a full ablation protocol. A uniform treatment protocol will be used in accordance with the manufacturer’s guidelines on the use of the device and the latest insights in the field of MR-HIFU treatment of uterine fibroids. Six months after treatment, a follow-up MRI scan will be performed before the follow-up appointment at the gynecologist (step 10 in Figure 1).

#### Control Group

The care as usual group will be offered surgery or UAE. Surgery will be either hysterectomy or myomectomy. Both hysterectomies and myomectomies can be performed by laparoscopy or laparotomy depending on the size and location of the fibroids. Participants allocated to the control group can decide together with their gynecologist which of the (minimally) invasive treatments they wish to undergo. All of the usual care treatments are performed extensively at the participating centers and will be performed according to national guidelines and local protocols. Surgery is preceded by a preoperative screening for anesthetic risk assessment. Depending on the modus of the hysterectomy or myomectomy, patients will be hospitalized for a minimum of 1-3 nights. UAE will be performed by well-trained and experienced radiologists. UAE can be either unilateral or bilateral. The patient usually has to stay in the hospital for 1-3 nights for careful pain monitoring after the procedure. Six weeks after all usual care treatments, a follow-up appointment at the gynecology department will be scheduled.

#### Use of Co-interventions

All included treatments aim for complete symptom reduction; however, clinical practice shows that additional treatment can be necessary during, for example, menstruation. Women can choose to use additional over-the-counter pain medication or prescribed medication such as oral contraception pills or antifibrinolytic drugs. These pills can influence symptom severity (both bleeding and pain). Therefore, data on the use of this medication are collected at both baseline and follow-up as part of the patient characteristics and medical consumption questionnaires.

### Data Collection

Data collection will take place before treatment, and at 3, 6, 12, and 24 months after treatment by questionnaires. Furthermore, baseline data of patient and treatment costs will be collected before treatment and after data lock-in (Table 1).

**Table 1 table1:** Timeline of data collection.

Data	Baseline	Treatment	3 months	6 months	12 months	24 months	Data lock-in
Informed consent	X						
Patient characteristics^a^	X						
Pregnancy outcomes^b^	X					X	
UFS-QoL^b,c^	X		X	X	X	X	
EQ-5D-5L^b,d^	X		X	X	X	X	
Onset of menopause^b^						X	
(Time to) reintervention^a^			X	X	X	X	X
Adverse events/complications^a^		X	X	X	X	X	
PREM^b,e^	X		X	X	X	X	
Recovery time^a^		X	X	X			
Medical Consumption Questionnaire^b,f^	X		X	X	X	X	
Productivity Costs Questionnaire^b,f^	X		X	X	X	X	
Costs of treatment^a^							X
Reason for not participating^a,g^	X						

^a^Retrieved from questionnaires and medical record.

^b^Retrieved from questionnaires solely.

^c^UFS-QoL: Uterine Fibroid Symptom and Quality of Life questionnaire.

^d^EQ-5D-5L: 5-level version of the EuroQoL Questionnaire.

^e^PREM: patient-reported experience measurement

^f^Used for the cost-effectiveness analysis.

^g^Data collected by the gynecologist in case of not willing to participate.

### Outcomes

#### Primary Outcomes

In the MYCHOICE study, primary outcomes include (1) QoL at the follow-up time point of 24 months after treatment and (2) cost-effectiveness of MR-HIFU.

QoL is commonly measured with the validated Uterine Fibroid Symptom and Quality of Life questionnaire (UFS-QoL) [29]. This questionnaire consists of 2 parts: 8 symptom questions and 29 questions concerning health-related QoL with 6 subscales. The 8 symptom severity questions concern duration, frequency and severity of menstruation, urination pattern, tightness or pressure in the pelvic area, and fatigue. The 6 subscales of the HR QoL part of the questionnaire are concern, activities, energy/mood, control, self-consciousness, and sexual function. All items are scored on a 5-point Likert scale. Both internal consistency reliability (subscale Cronbach α=.83-.95, overall health-related QoL score α=.97) and test–retest reliability (intraclass correlation coefficients 0.76–0.93) of this questionnaire were shown to be adequate. Moreover, the UFS-QoL has an excellent construct and discriminative validity [29]. From the symptom-specific part of the questionnaire, a symptom severity score (SSS; range 0-100, with higher scores indicating more [severe] symptoms) can be calculated. Because symptom reduction is the main aim of all uterine fibroid treatments, we define QoL at the follow-up time point of 24 months as a change in reported symptom severity compared with baseline.

The cost-effectiveness analysis will be performed from a societal perspective. Cost-effectiveness will be reported as incremental cost-effectiveness ratio, that is, the ratio between the expected difference in cost and the expected difference in effect (clinical effect or utility [quality-adjusted life year] and net [monetary] benefit). Cost-effectiveness acceptability curves will be presented to summarize the impact of uncertainty on the result of the economic evaluation.

The Dutch value set will be applied to the 5-level version of the EuroQoL questionnaire (EQ-5D-5L) to produce quality-adjusted life year values [30].

We consider 4 cost categories: (1) direct medical in-hospital costs (eg, preprocedural costs, in-hospital costs related to the intervention, any additional in-hospital medical costs during follow-up); (2) direct medical out-of-hospital costs (eg, unscheduled general practitioner visits and use of medication out of hospital); (3) direct nonmedical costs (patient expenses such as travel costs and sanitary measures); and (4) indirect costs (productivity-related costs due to absence from work) [31].

The unit costs of direct medical in-hospital cost volumes will be based on Dutch guidelines for economic evaluations. The cost volumes of MR-HIFU, UAE, myomectomy, and hysterectomy are based on detailed microcosting by using data recorded in the case record forms and patient records in all participating hospitals. The cost volumes related to complications will be recorded prospectively in the case record form (eg, type of complication, unscheduled outpatient visit, subsequent diagnostic and therapeutic measures). All interventions include 1 follow-up by phone (at 1 week after primary intervention; Figure 1). In case of an UAE, myomectomy, and hysterectomy, 1 follow-up visit at the outpatient gynecology department will be planned at 6 weeks after the primary intervention; in case of MR-HIFU at 3 and 6 months, a follow-up appointment at the gynecology department will take place, at 6 months combined with an MRI scan. This will be considered standard care, and will therefore be included in our cost analysis. Any further follow-up visits conducted for study purposes will be excluded from our analysis unless these are unscheduled follow-up visits for medical problems related to the primary intervention.

The unit costs of direct medical out-of-hospital costs, direct nonmedical costs, and indirect costs will also be based on Dutch guidelines for cost calculations in health care. The following altered patient questionnaires will be used: iMTA Productivity Cost Questionnaire (iPCQ) and iMTA Medical Consumption Questionnaire (iMCQ). The iPCQ questionnaire is a short generic measurement instrument on the impact of disease on the ability of a person to perform work. It also contains questions about absence from unpaid labor. This questionnaire is a generic instrument for measuring medical costs, including questions related to frequently occurring contacts with health care providers. All questionnaires will be sent by email or post according to the preference of the participant at baseline and at 3, 6, 12, and 24 months after treatment (Table 1). Patients will receive an automatic reminder by email. Indirect costs due to absence from work will be estimated as the actual working time lost (hours) multiplied by the average net income according to the friction cost method.

A decision analytic model with lifetime horizon will be developed by combining costs and effects. Complete uncertainty analyses (deterministic and probabilistic sensitivity analyses) will be performed.

In addition, a budget impact model will be constructed, taking the (gradual) implementation of MR-HIFU over time, the initial investments, and the savings into account that were shown to be realistic in the trial. The model will use different perspectives: (1) The net Dutch Budgetary Framework for Healthcare (Budgettair Kader Zorg) perspective; and (2) health insurance/third-party payer perspective.

The budget impact model is performed through modeling and analyzed in a probabilistic way.

Because MR-HIFU is an outpatient treatment with a fast(er) recovery, it is expected to be cheaper than the current standard (minimally) invasive treatments, especially from a societal perspective.

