#### Secondary Outcomes

Data on several secondary outcomes will be collected (Table 2). These include adverse events and complications during treatment and recovery, cost-effectiveness–relevant outcomes such as hospital stay duration and use of (co)medication, patient-reported experiences, reintervention rate in case a uterine-sparing treatment was performed, reproductive outcomes when applicable, and technical outcomes after MR-HIFU, such as NPV reached.

**Table 2 table2:** Secondary outcomes of the MYCHOICE^a^ study, including measurement tool and statistical analyses.

Outcome	Description	Measurement	Statistical analyses
QoL^b^ parameters	QoL is expected to be negatively correlated with symptom severity. When symptoms decrease, the QoL is expected to improve.	UFS-QoL^c^ questionnaire and EQ-5D-5L^d^ questionnaire.	The time course of the change in health-related quality of life after treatment will be analyzed using longitudinal covariance analysis similar to the analysis of the change in SSS^e^.
Adverse events and complications	The nature of adverse events and complications of the 2 treatment arms are expected to differ.	Adverse events will be classified according to the classification of surgical complications [32].	Adverse events are analyzed using descriptive statistics. Adverse events per treatment group and treatment will be presented with their occurrence rate.
Length of hospital stay	Reduced hospital stay is beneficial in terms of health care costs and is also considered as a great advantage by patients.	Length of hospital stay will be collected from the patient hospital file.	The average length of the hospital stay will be reported as mean (SD) or median (interquartile range).
Periprocedural and postprocedural pain	Pain perception may influence treatment experience and therefore satisfaction with the treatment.	Periprocedural and postprocedural pain will be measured on a numerical rating scale from 0 to 10 in the 3 months’ follow-up questionnaire. Pain complaints at 3, 6, 12, and 24 months after treatment will be registered by the amount and duration of pain killers used.	The numerical rating score is considered to be a semicontinuous measure (range 0-10: higher score represents more pain). Pain experienced will be reported as mean (SD) or median interquartile range.

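### Adverse-event rates by arm may partly reflect unequal follow-up contact: control women are seen at 6 weeks, MR-HIFU women not until 3 months

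*Protocol article*

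**What the plan says.** All places are in the Protocol article.

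- **Shared contact.** Primary Outcomes: "All interventions include 1 follow-up by phone (at 1 week after primary intervention; Figure 1"). The questionnaires at 3, 6, 12 and 24 months are also the same in both arms (Data Collection).
- **Control arm.** Primary Outcomes sets both schedules in one sentence, with the control arm's only clinic visit "planned at 6 weeks after the primary intervention; in case of MR-HIFU at 3 and 6 months, a follow-up appointment at the gynecology department". The Control Group section agrees: "Six weeks after all usual care treatments, a follow-up appointment at the gynecology department will be scheduled". No later routine visit is described.
- **MR-HIFU arm.** The same sentence in Primary Outcomes pairs the second of these visits with an MRI scan. The MR-HIFU section agrees: "Six months after treatment, a follow-up MRI scan will be performed before the follow-up appointment at the gynecologist".
- **Source of harm data.** Table 1 lists adverse events/complications at treatment and at 3, 6, 12 and 24 months, with the footnote "Retrieved from questionnaires and medical record". Safety Reporting counts both what participants report and what the investigator or staff observe.
- **Definition.** Safety Reporting restricts adverse events, serious ones included, to those in the first 30 days after treatment that are related to taking part.
- **Analysis.** Table 2 is descriptive: "Adverse events per treatment group and treatment will be presented with their occurrence rate".

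**The concern.** When one source of a harm rate is what clinicians write down, and the arms meet clinicians on different schedules, the recorded rates can differ even if the true rates do not. A mild complication in week 3 can be noted at the control arm's 6-week visit, while it is still recent. In the MR-HIFU arm the same event waits for the 3-month visit or questionnaire, unless the woman seeks unscheduled care. That gap would flatter MR-HIFU, in an open trial of a treatment expected to bring faster recovery.

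If events after day 30 are also counted, there is a second gap in the opposite direction: from 3 to 6 months MR-HIFU women have routine visits and an MRI scan, and control women have neither.

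No between-arm test of harms is planned, but rates set out by arm will be read side by side. Unequal detection distorts a descriptive rate as much as a tested one. It cannot be examined afterwards unless the source of each event was recorded.

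**Working it through.** **1. The plan's own figures.** The article states no adverse-event rate, detection rate or power for harms, so there is no harm figure to reproduce. The arm sizes used in step 5 do reproduce: (1 + 1/2) x (1.960 + 1.282)^2 x 20^2 / (15 - 5)^2 = 63.04, rounded up to 64 control and 128 MR-HIFU. Dividing by 0.8 gives 80 and 160.

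**2. Scheduled contacts against the 30-day window.** Months are converted to days approximately.

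| Contact | Day | Arm | Within 30 days? |
|---|---|---|---|
| Telephone call | 7 | both | yes |
| Clinic visit | 42 | control | no |
| Questionnaire | 91 | both | no |
| Clinic visit | 91 | MR-HIFU | no |
| Questionnaire | 182 | both | no |
| Clinic visit with MRI | 182 | MR-HIFU | no |

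Every arm-specific contact falls after day 30. Under the Safety Reporting definition these contacts cannot find a newly occurring adverse event. They can only prompt late recording of an earlier one. For an event on days 8-30, the first scheduled clinic visit comes 12 to 34 days later in control (42 - 30; 42 - 8) and 61 to 83 days later in MR-HIFU (91 - 30; 91 - 8).

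**3. How much of the window is exposed.** Days 8-30 are 23 of 30 days (77%). Onset is unlikely to be uniform. If it decays exponentially with mean tau (an assumption), the share of 30-day events after day 7 is [exp(-7/tau) - exp(-30/tau)] / [1 - exp(-30/tau)]. For tau = 3, 5, 7, 10 and 15 days this gives 10%, 24%, 36%, 47% and 57%.

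**4. Size of a spurious difference.** Take the same true rate p of exposed events in both arms and capture probabilities c for control and h for MR-HIFU. The recorded difference is p x (c - h). All values of p, c and h are assumptions. Each cell shows the recorded control rate, the recorded MR-HIFU rate and the difference in percentage points.

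| True rate | Capture 95% vs 90% | Capture 90% vs 80% | Capture 90% vs 60% |
|---|---|---|---|
| 10% | 9.5, 9.0: 0.5 | 9.0, 8.0: 1.0 | 9.0, 6.0: 3.0 |
| 20% | 19.0, 18.0: 1.0 | 18.0, 16.0: 2.0 | 18.0, 12.0: 6.0 |
| 30% | 28.5, 27.0: 1.5 | 27.0, 24.0: 3.0 | 27.0, 18.0: 9.0 |

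If 10-30% is instead read as the rate of all 30-day events, only the exposed share from step 3 is affected. The range then shrinks to between 0.5 x 0.10 = 0.05 and 9 x 0.77 = 6.9 points.

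**5. Against sampling error.** The 95% half-width of the difference is 1.96 x sqrt[pc(1 - pc)/80 + ph(1 - ph)/160], where pc and ph are the recorded control and MR-HIFU rates. Over the cells above it runs from 7.3 to 12.0 points. For 18% vs 12% it is 9.8. In every cell the spurious difference is smaller than the half-width.

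**6. The window itself.** Safety Reporting stops at 30 days, while Table 1 collects adverse events/complications to 24 months. The article does not say which of these enter the Table 2 rates. Whether the 3- and 6-month visits and the MRI can add events to the MR-HIFU rate depends on that answer.

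**The case against.** The strongest reply is that much of the harm record is already common to both arms: the 1-week call, identical questionnaires that cover medical consumption, and prospective recording of complications with unscheduled visits and treatment. Table 1 has no 6-week collection point, so that visit contributes only through what the clinician happens to write. Postprocedural pain, a likely minor event, is measured separately in the 3-month questionnaire. The outcome is secondary and descriptive, and the two arms' events are expected to differ in nature anyway. All of this stands. It narrows the concern to minor events that never led to unscheduled care, but the clinic record remains an unequal source.

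A reader might go further in three ways that the documents do not support.

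- *That the MRI and later visits inflate MR-HIFU harms.* Under the 30-day, related-only definition they cannot add new events. The inference needs the 24-month complications to be counted, which the article does not settle.
- *That MR-HIFU gains a false advantage of a given size, such as 6 points.* That figure is the product of an assumed 20% rate and an assumed capture gap of 30 points. Milder assumptions give 1 point or less.
- *That the cost-effectiveness result is biased.* Complication costs follow resource use, and a minor event merely mentioned at a routine visit adds little. The article treats these visits as standard care, so the costs they prompt arguably belong to the strategy.

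A separate asymmetry lies inside the 30 days: usual-care patients typically stay 1-3 nights in hospital, while MR-HIFU is an outpatient treatment. It also bears on ascertainment, but it concerns the first days and does not come from the visit schedule.

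**Conclusion.** The point holds in a limited form. Scheduled clinical contact after the first week differs by arm, the medical record and staff observation feed the adverse-event data, and rates are presented by arm with nothing that restricts or separates them by source. The rates may therefore partly reflect unequal ascertainment; the documents do not show that they do.

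Under the 30-day definition, the effect of the schedules is confined to minor events on days 8-30 and would tend to favour MR-HIFU. If the complications collected to 24 months also enter the rates, an opposite effect is added and the net direction is unknown.

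The size is unknown. The range of about 0.5 to 9 points rests wholly on assumed true rates of 10-30% and assumed capture gaps, and its upper end needs a large gap. The primary symptom-severity analysis and the sample size are untouched. This is a cheap improvement to a secondary outcome, not a flaw in the main comparison.

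**What to change.** Leave the clinic visits and the MRI as they are.

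1. Reconcile Table 1 with Safety Reporting, so that one stated window applies to the rates in Table 2. Which window is for the sponsor to decide.
2. Send one short adverse-event checklist to both arms at 6 weeks through the existing questionnaire system, and put the same items in the later questionnaires.
3. Add a case-report-form field for the source of first detection: call, questionnaire, unscheduled care, arm-specific visit or 6-month MRI.
4. Keep all events in the main rates. Add a by-arm sensitivity table restricted to sources common to both arms, and show separately the events first found at an arm-specific visit or the MRI. Dropping those events from the main rates would be too strong, because a true early complication first noted at the 6-week visit could be lost.

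The cost is one short electronic questionnaire, one data field, a wording change and one extra table, with slightly more burden on participants. No visits or patients are added. Women already past 6 weeks when the checklist starts cannot complete it, so it should start on the same date in both arms. The checklist does not remove the difference in inpatient observation.

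### Productivity costs in a primary economic outcome are priced at net income despite a societal perspective and a guideline-based rule; separately, utility is not read between baseline and 3 months, with an effect of unknown direction

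*Protocol article*

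**What the plan says.** All references are to the Methods of the protocol article.

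- **Status and perspective.** Primary Outcomes lists "2) cost-effectiveness of MR-HIFU" beside 24-month quality of life and states: "The cost-effectiveness analysis will be performed from a societal perspective".
- **Scope of productivity costs.** The fourth cost category is "4) indirect costs (productivity-related costs due to absence from work").
- **Price of a lost hour.** Two rules appear in one paragraph of Primary Outcomes. The general rule is that unit costs of "indirect costs will also be based on Dutch guidelines for cost calculations in health care". The specific rule is that absence is "estimated as the actual working time lost (hours) multiplied by the average net income according to the friction cost method".
- **Utility.** QALYs come from the EQ-5D-5L with the Dutch value set. Data Collection gives the schedule: "Data collection will take place before treatment, and at 3, 6, 12, and 24 months after treatment by questionnaires". Table 1 agrees, with no EQ-5D-5L between baseline and 3 months.
- **Early contact.** "All interventions include 1 follow-up by phone (at 1 week after primary intervention; Figure 1").
- **Expectation.** Primary Outcomes expects MR-HIFU to cost less because recovery is quicker, above all from society's viewpoint. Statistical Methods also allows that symptoms may fall faster in the usual care arm, because of hysterectomy.

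**The concern.** **Price.** From a societal perspective, a lost working hour costs the output forgone, for which the usual proxy is the full cost of that hour of labour. Income tax and social contributions are transfers within society; they do not make the lost output smaller. Net income is the worker's loss, not society's. The friction cost method limits how long an absence is counted and gives no reason to price the counted hours at take-home pay. An analyst could defend either the guideline price or the net-income price from the text, and the choice changes the incremental cost, the incremental cost-effectiveness ratio and the acceptability curve.

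**Utility.** The arms are expected to differ most in the first weeks: an outpatient procedure against surgery or embolization with nights in hospital. No utility is recorded in that period. A change that has come and gone by 3 months leaves no trace in the trial's own utility readings.

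**Working it through.** **The plan's own figures.** No figure is stated for the economic outcome. The one reproducible figure is the sample size for the symptom score. With margin 15, assumed difference 5, SD 20, one-sided alpha 0.025, power 90% and 2:1 allocation, control n = (1 + 1/2) × 20² × (1.960 + 1.282)² / (15 − 5)² ≈ 63.0, rounded up to 64. MR-HIFU is then 128 and the total 192. Dividing by 0.8 gives 80 + 160 = 240. This matches the Sample Size section, and nothing below changes it.

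**Price of a lost hour.** Let ΔH be the between-arm difference in counted hours, p the full labour cost per hour, and r the ratio of net pay to labour cost.

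- Difference at full labour cost: p × ΔH.
- Difference as written: r × p × ΔH.
- Share lost: 1 − r, whatever p and ΔH are. The friction limit acts on the hours, so it cancels.

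The document gives no r. Over an assumed range:

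| r (assumed) | share of productivity cost lost |
|---|---|
| 0.8 | 20% |
| 0.7 | 30% |
| 0.6 | 40% |
| 0.5 | 50% |

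The error shrinks the difference towards zero. If MR-HIFU does bring fewer lost hours, as the protocol expects, its saving is understated.

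**Utility before 3 months.** Assume for illustration that utility falls by d at treatment, returns after w weeks to the straight line joining the baseline and 3-month readings, and that QALYs are computed along that line. The amount missed per patient is d × w / 52 for a constant dip and d × w / 104 for one that fades linearly. All values of d and w are assumptions.

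- Fading: 0.1 × 2 / 104 = 0.002 up to 0.3 × 6 / 104 = 0.017 QALY per patient.
- Constant: 0.1 × 2 / 52 = 0.004 up to 0.3 × 6 / 52 = 0.035 QALY per patient.

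What matters for the comparison is the difference between arms. Two examples with fading dips:

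- 0.05 for 1 week against 0.2 for 2 weeks: (0.4 − 0.05) / 104 = 0.003 QALY.
- 0.1 for 1 week against 0.3 for 6 weeks: (1.8 − 0.1) / 104 = 0.016 QALY.

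In both examples the interpolated difference from these dips is zero. The formula works equally in reverse: an early rise above the line in the usual care arm, such as quick relief after hysterectomy, contributes the same kind of term with the opposite sign. The document gives no basis for saying which is larger.

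**The case against.** **Loose wording.** Net income may be a slip, since the same paragraph commits indirect costs to national guidelines. If the analyst follows the guideline, and its hourly price is a labour cost, there is no bias. What the guideline price contains cannot be checked from the article. This makes the problem cheap to cure, but it does not remove it, because the specific sentence says something else.

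**The error is conservative.** Underpricing hours works against the sponsor's own expectation that MR-HIFU is cheaper, so it would not manufacture a favourable result. That is correct. A cost-effectiveness ratio is nevertheless an estimate, and a known understatement in it is still an error.

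**Recovery is measured.** A reader might infer that the economic evaluation misses recovery altogether. It does not. Table 1 collects recovery time, complications, and work absence and care use reported at 3 months; hospital stay comes from the hospital file. The lost hours are counted. Only their price, and the early utility, are in question.

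**QALY method not stated.** The article does not say how readings become QALYs. That may be in an analysis plan not shown, and the planned decision model could include a recovery decrement. This stands, so straight-line interpolation above is an assumption. No analysis plan, however, can supply readings that were not taken.

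**Direction.** A reader might infer that the QALYs are biased against MR-HIFU. The statement on hysterectomy in Statistical Methods points the other way, and MR-HIFU may have a dip of its own. The sign cannot be settled from the document.

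**Pain score.** "Periprocedural and postprocedural pain will be measured on a numerical rating scale from 0 to 10 in the 3 months" follow-up questionnaire. A reader might add this to the economic case. It is a secondary outcome that enters neither costs nor QALYs. Late recall in an open trial is a separate weakness, of unknown direction.

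**Conclusion.** The pricing point holds. The net-income sentence conflicts with the declared societal perspective and is not reconciled with the guideline rule beside it. Followed literally, it understates productivity costs, and their difference between arms, by 1 − r: 20-50% for an assumed r of 0.5-0.8. A euro amount per woman would also need hours lost, employment and an hourly cost. The document gives none of these, so none is claimed here.

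The utility point holds as a gap in observation, not as a signed bias. Between-arm amounts of about 0.003-0.016 QALY are illustrations under assumed dips and straight-line interpolation. The sample size and the symptom-score analysis are unaffected.

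**What to change.** 1. **Price.** Replace net income with gross labour cost per hour, including employer contributions, and keep the friction cost method. State that this is the price used under the guideline rule, so that the paragraph contains one rule. Cost: one sentence and no new data; it applies to all women already enrolled, because their hours are collected anyway.

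2. **Early utility.** For women not yet treated, add a short EQ-5D-5L at the existing 1-week phone contact and one by email at about 6 weeks, in both arms and on the same schedule. For women who lack these readings, add a sensitivity analysis that varies the early utility path by arm, including faster relief after hysterectomy. Cost: slight patient burden and a cohort with a mixed schedule. If no women remain to be treated, report the gap as a limitation, without a stated direction, and run the sensitivity analysis alone.
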